**Methods/Design:**

The overall objective of this 5-year study is to evaluate a health literacy-informed, electronic health record-based strategy for promoting safe and effective prescription medication use in a primary care setting. A total of 600 English and Spanish-speaking patients with diabetes will be consecutively recruited to participate in the study. Patients will be randomized to receive either usual care or the intervention; those in the intervention arm will receive a set of print materials designed to support medication use and prompt provider counseling and medication reconciliation. Participants will be interviewed in person after their index clinic visit and again one month later. Process outcomes related to intervention delivery will be recorded. A medical chart review will be performed at 6 months. Patient outcome measures include medication understanding, adherence and clinical measures (hemoglobin A_1_c, blood pressure, and cholesterol; exploratory outcomes only).

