## Methods/Design

This study seeks to reduce the patient confusion that often leads to unintentional medication non-adherence or medication errors. To promote sustainability and dissemination, we are utilizing an electronic health record platform to automate the delivery of patient-centered medication information materials. The specific aims of the study are as follows: (1) to refine and field test an electronic health record strategy for generating and distributing low-literacy prescription information for English- and Spanish-speaking primary care patients with diabetes; (2) to assess the process of the electronic health record intervention and its fidelity for providing understandable and actionable prescription information for patients at the point of prescribing; and (3) to evaluate the effectiveness of the electronic health record-based strategy to improve medication understanding, reconciliation, regimen consolidation, and adherence, compared with standard care. We have an additional exploratory aim to examine the effect of the intervention on surrogate clinical outcomes; hemoglobin A_1_c, low-density lipoprotein cholesterol and blood pressure.

This study is being conducted at the University of Illinois Hospital and Health Sciences System, an urban, academic medical center located in Chicago, which uses Cerner Powerchart®, a common electronic health record system. Patients are enrolled from three primary care sites: a resident-staffed general medicine clinic, a medicine/pediatrics clinic, and a faculty primary care clinic. These clinics serve a diverse, low-income patient population that is approximately 65% African American and 20% Hispanic. An estimated 36% of general medicine clinic patients have limited health literacy. Adjusted for patient volume, approximately 25% of these low literacy patients have been diagnosed with diabetes. The current standard of care in this clinic is for patients to receive a basic after-visit summary that describes the medical visit and includes a list of medications prescribed to the patient according to the electronic health record. This summary has not been designed according to health literacy best practices and patient education materials are not routinely given as part of standard care.

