We will recruit 600 patients from participating clinics in no set proportion and randomize each to receive either standard care or the intervention. Participants will be eligible if they: (1) are over 18 years old; (2) have a documented diagnosis of diabetes; (3) are currently taking at least three daily, chronic, non-PRN (not pro re nata) medications; (4) speak English or Spanish; (5) have no intention to change clinics within the next year; (6) score 4 or higher on a six-item cognitive screener [7]; (7) are, by self-report, primarily responsible for taking their own medications; and (8) were prescribed a new medication, or have a dose, refill, or frequency change of a current medication for hypertension, hyperlipidemia, or diabetes mellitus during their index clinic visit.

Potentially eligible patients (criteria 1 to 4 above) are first identified via a review of their electronic health records. A list of those patients with a clinic appointment scheduled within the next three months is then compiled and sent to clinic physicians via secure email. Physicians have the opportunity to indicate which potentially eligible patients should not be contacted, owing to severe illness or cognitive concerns. With physician approval, patients will be approached by the research assistant to confirm eligibility following their doctor’s appointment. Research assistants will speak with potential participants after receiving an electronic message that they have been prescribed a new medication or received a changed dose or frequency of a medication of interest. Eligibility criteria will be confirmed before patients provide written consent and are enrolled into the study. The study has been approved by institutional review boards at the University of Illinois in Chicago (2012–0262) and Northwestern (STU00064056) and is also registered on clinicaltrials.gov (NCT01669473).

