Patients in the intervention arm will receive three electronic health record-generated items at their clinic visit: (1) a pre-visit medication list, (2) medication information sheets, and (3) a post-visit medication list. These materials were designed by study team members and incorporate health literacy best practices, with Lexile analyses confirming a readability level of <8th grade [8,9]. The medication sheets and pre-visit medication list were previously tested in a National Institutes of Health study (R18HS17220). All materials were translated into Spanish using a committee-based approach and pilot tested among English- and Spanish-speaking patients (*N* = 9) to ensure comprehensibility [10]. The materials are as follows:The pre-visit medication list is generated on check-in and includes all medications prescribed to the patient according to their electronic health record. It lists the dosage, frequency and indication for all medications. The instructions on the form ask patients to report how much of each medication they take on a daily basis and if they have any concerns (need refill, cost, and so on) for any of the drugs. Patients are then asked to add any additional prescription or over-the-counter medications they are using and to remove medications that they are no longer taking. Forms are designed to be shared with providers during the clinic visit to promote medication reconciliation.If the patient is prescribed a new or dose-adjusted medication for diabetes, hyperlipidemia, or hypertension, a medication information sheet for that medicine will print automatically in the patients’ preferred language (English or Spanish). The medication information sheet is a one-page, plain-language information sheet that describes the medication’s indication for use, general directions, and side effects. It is designed to be patient-friendly and to provide essential need-to-know information for each drug.Following the visit, patients receive an updated post-visit medication list, which reflects any changes made to the pre-visit medication list as a result of their visit that day. The post-visit medication list includes all of the patient’s medications, listing dosage, indication, and the times each medication should be taken. It is intended to help patients organize their regimen according to the Universal Medication Schedule [11]. The Universal Medication Schedule ‘grounds’ medication use by providing more explicit times to describe when medicine should be taken (morning, noon, evening, bedtime) [5]. This concept was reviewed and recommended by the Institute of Medicine, the US Pharmacopeia, and the National Council for Prescription Drug Programs as a health literacy best practice. Patients in the intervention arm will receive this post-visit medication list, while those in usual care will receive a standard ‘after-visit summary’ recently implemented at the University of Illinois Hospital and Health Sciences System to comply with meaningful use requirements [12]. This standard after-visit summary is the only educational print material that patients in the usual care arm routinely receive after their clinic visit.

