### Key covariates

We will collect data on a number of key covariates, including age, sex, English proficiency, comorbidities, medication and healthcare utilization, income, and race and ethnicity. Health literacy will be measured using the Newest Vital Sign [27].

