### Analyses

A sample size of 600 patients, 300 in each arm, was determined for this research study based on sample size calculations for the outcome measure of medication understanding. Assuming an overall baseline rate of understanding of 65%, a sample of 300 patients per arm would enable the detection of an 11% absolute increase in medication understanding with 80% power. These differences were considered appropriate, based on the results of prior studies conducted by this study team [17,28,29]. This sample size also supports our exploratory analyses for the effects of the intervention on surrogate clinical outcomes. For example, a sample size of 600 provides adequate power (86%) to detect a difference of 3 mm Hg in mean systolic blood pressure by study arm, assuming a standard deviation of 12.

We will perform intent-to-treat analyses to determine the study results. Before conducting formal analyses, we will perform descriptive statistics to ensure adequate balance of patient characteristics across the two treatment arms (usual care and intervention) at baseline; *t* tests and *χ*^2^ tests will be used to evaluate differences across the two arms for continuous and binary variables, respectively. Generalized linear models will be used for data analyses using PROC GENMOD in SAS (version 9.2), specifying the logit link function for binary outcomes (medication understanding, reconciliation, adherence, and regimen consolidation) and the identity link function for continuous outcomes (blood pressure, hemoglobin A_1_c). The treatment group will be the independent variable of primary interest and will be modeled with usual care specified as the reference group. Any potential confounding covariates noted in the descriptive analysis will also be included in the models.

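### The stated outcome models have no clinic or physician term, so their intervals may be too narrow for a general claim about the strategy if its effect varies between physicians

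*Protocol article*

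**What the plan says.** **Design.** Randomisation is by patient, with no fixed clinic shares: "We will recruit 600 patients from participating clinics in no set proportion and randomize each to receive either standard care or the intervention". The sites differ in staffing: "Patients are enrolled from three primary care sites: a resident-staffed general medicine clinic, a medicine/pediatrics clinic, and a faculty primary care clinic".

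**Mechanism.** The Abstract describes the materials as "designed to support medication use and prompt provider counseling and medication reconciliation". On the pre-visit list, Methods/Design adds: "Forms are designed to be shared with providers during the clinic visit to promote medication reconciliation". The section on medication reconciliation likewise presents that list as a prompt to communication between physician and patient. Process outcomes include whether the materials led to such discussion.

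**Model.** The Analyses section names PROC GENMOD, a logit link for the binary outcomes and an identity link for the continuous ones. It then states: "The treatment group will be the independent variable of primary interest and will be modeled with usual care specified as the reference group". Further covariates enter if the descriptive comparison of the arms marks them as potential confounders. The covariate section begins "We will collect data on a number of key covariates, including age, sex, English proficiency, comorbidities" and goes on to name only patient-level variables. Nothing is said of a clinic term, a physician term, a repeated statement, a random effect or a robust variance.

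**Sample size.** "a sample of 300 patients per arm would enable the detection of an 11% absolute increase in medication understanding with 80% power", from an assumed rate of 65%. No design effect is mentioned.

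**Reach.** The Discussion presents the strategy as a possible model for other ambulatory settings and as something that health centres nationwide could adopt.

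**The concern.** When part of an intervention works by prompting a provider to act, its effect may differ between providers who take up the prompt and those who do not. Residents and faculty may also differ in this respect. The process outcome on physician-patient discussion shows that the investigators themselves treat uptake as an open question.

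The stated model treats the 600 patients as independent. Its standard error describes the average effect among the physicians who happened to take part. A claim about the strategy in general practice also carries the uncertainty from which physicians were sampled, and that component is missing. A result driven by a few engaged physicians would not show in the width of the interval.

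Clinic is a smaller, separate matter. It is a known structural feature of the trial, yet it would enter the model only if a comparison of the arms happened to flag it. Whether the analysis is adjusted for clinic would then be settled by the data and not in advance.

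**Working it through.** **Step 1: the plan's own figures.** A two-sided 5% test is assumed, since the article gives no alpha. With 300 independent patients per arm:

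- 65% v 76%: power 84.2% without continuity correction, 81.9% with it.
- Reading 65% as the overall rate (59.5% v 70.5%): power 80.8%.
- Systolic pressure, difference 3 mm Hg, SD 12: power 86.5%, against the stated 86%.

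The stated 80% is matched within 2 points by the second and third versions of the calculation. The sample size therefore rests on independent patients with no design effect.

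**Step 2: no variation in effect.** With patient-level randomisation, differences in level between physicians largely cancel between arms. In simulation with an intercept SD of 0.5 on the logit scale and a constant effect, the ratio of true to model standard error is 0.97 to 0.99 and the type I error 4.3% to 4.8%. Shared physicians alone do no harm.

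**Step 3: effect varies between physicians.** Let tau be the SD between physicians of the risk difference and K the number of physicians, with equal caseloads. Then approximately

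Var(difference) = V + tau²/K, where V is the independent-patient variance.

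Under no average effect at 65%, V = 2 × 0.65 × 0.35 / 300 = 0.001517. A log-odds effect SD s corresponds to tau ≈ s × 0.65 × 0.35:

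- s = 0.3: tau ≈ 0.068
- s = 0.5: tau ≈ 0.114

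The ratio of true to model standard error is r = √(1 + tau²/(K·V)), and the true type I error is 2 × [1 − Φ(1.96/r)].

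Example with s = 0.5 and K = 20: tau²/K = 0.01294/20 = 0.000647; r = √(1 + 0.000647/0.001517) = 1.194; 1.96/1.194 = 1.64; type I error 10.1%.

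| K (assumed) | s = 0.3: r | s = 0.3: type I error | s = 0.5: r | s = 0.5: type I error |
|---|---|---|---|---|
| 20 | 1.07 | 6.8% | 1.19 | 10.1% |
| 40 | 1.04 | 5.9% | 1.10 | 7.5% |
| 60 | 1.02 | 5.6% | 1.07 | 6.7% |
| 100 | 1.01 | 5.4% | 1.04 | 6.0% |

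Simulation with a physician intercept SD of 0.4 agrees. At s = 0.3 it gives 6.8%, 5.9%, 5.5% and 5.4% for 20, 40, 60 and 100 physicians. At s = 0.5 it gives 10.2%, 7.7% and 6.6% for 20, 40 and 60. A physician-clustered robust test brings the rate back to about 5% to 6%.

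**Step 4: what honest intervals cost.** At 65% v 76%, V = (0.65 × 0.35 + 0.76 × 0.24)/300 = 0.001366, so the standard error is 0.037. Power for the 11-point effect is Φ(0.11/√(V + tau²/K) − 1.96). With tau = 0 it is 84.5%. With tau = 0.10 it is 62% for K = 10, 72% for K = 20, 76% for K = 30, 80% for K = 60 and 82% for K = 100.

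**The case against.** The strongest reply is that the model fits the design. Patients are individually randomised, the test is valid if the materials affect no one, and the standard error is about right for the average effect in the participating physicians. The Analyses section names no wider target, and the dissemination language is in the Discussion. This stands, and it limits the point to the wider claim. A reader might infer that 600 patients under shared physicians need the usual cluster design effect, or that the stated test is invalid. The documents do not support that.

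Second, a reader might infer that the intervention works only if the physician acts, or that its effect must differ between physicians. That goes beyond the text. The medication sheet prints automatically, the post-visit list is for the patient's own use, and the pre-visit list is filled in by the patient. Medication understanding, which sizes the trial, is a patient demonstration and lies closest to those items. The physician's role is most direct for reconciliation. Variation is plausible, not documented.

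Third, the assumed spreads may be generous. At a 65% base, one SD of 0.5 on the log-odds scale is about +10 or −12 points, as large as the whole target effect. A resident-staffed clinic may also supply many physicians, and with 60 to 100 of them the inflation is small. Both points stand, so the result can only be given as a range.

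Fourth, the article condenses a fuller plan, its covariate list is not presented as exhaustive, and clinic could enter as an observed confounder. The fuller plan may indeed say more. The article is not merely silent, though: it states the procedure, the main term and a covariate rule. Under that rule clinic would enter only through the observed data, and doing so would not address variation between physicians.

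A reader might also conclude that allocation should now be stratified by clinic. The article does not describe the allocation method, and recruiting in no set proportion concerns clinic shares, not balance between arms. There is no basis for asking for a change.

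**Conclusion.** The point holds as a conditional one. The stated model is sound for the average effect among the participating physicians. It gives intervals that are too narrow for a claim about the strategy in general if the effect varies between physicians, a possibility that the described mechanism makes reasonable to guard against.

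The size cannot be fixed from the documents. Over 20 to 100 physicians, the true type I error of a nominal 5% test is about 5% to 7% at a log-odds effect SD of 0.3 and about 6% to 10% at 0.5. The upper ends belong to 20 physicians. With no variation it is nominal or slightly below. These figures assume two-sided 5%, equal caseloads, a 65% base rate and the stated ranges for the number of physicians and the effect SD.

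The missing clinic term does not inflate type I error. It is a modest loss of precision and leaves to the data a choice that is easily made in advance.

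**What to change.** 1. Prespecify clinic as a fixed effect in every outcome model, whatever the observed balance. This costs almost nothing. It adjusts for differences in level between clinics and does not deal with variation in effect.
2. Record the index-visit physician for each participant.
3. Prespecify a physician-clustered analysis with robust variance and a small-sample correction, at least as a sensitivity analysis and chiefly for reconciliation. PROC GENMOD can fit this by generalized estimating equations with physician as the cluster. The correction, such as a t reference with K − 1 degrees of freedom, should be written out and not assumed to come with the default output.
4. State whether the treatment effect is meant for the participating physicians or for physicians more widely, so that the reader knows which interval supports which claim.

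The data cost is one variable, and enrolment was still open when the article was written. If effects are constant, little is lost. If they vary between a small number of physicians, the intervals widen and real power falls, for example from 84.5% to 72% with 20 physicians at a risk-difference SD of 0.10. No change to the allocation is requested.

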
We will interview each patient in person at baseline, immediately following the index clinic visit, and one month after the index visit. At 6 months, a chart abstraction will be conducted to extract clinical surrogate outcome data (hemoglobin A_1_c, blood pressure, and low-density lipoprotein cholesterol).

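### Adjustment covariates are picked from a baseline balance check instead of being fixed in advance, so chance imbalance, not prognostic strength, decides what enters each model

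*Protocol article*

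**What the plan says.** The Analyses section sets out a sequence. Before the formal analyses, "we will perform descriptive statistics to ensure adequate balance of patient characteristics across the two treatment arms". For this, t and chi-square "tests will be used to evaluate differences across the two arms for continuous and binary variables, respectively". Generalized linear models follow, with a logit link for the four medication outcomes and an identity link for blood pressure and hemoglobin A1c. On the content of those models it says: "The treatment group will be the independent variable of primary interest and will be modeled with usual care specified as the reference group". It then adds the selection rule: "Any potential confounding covariates noted in the descriptive analysis will also be included in the models". No other route into a model is described.

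The Key covariates section states: "We will collect data on a number of key covariates, including age, sex, English proficiency, comorbidities, medication and healthcare utilization, income, and race and ethnicity". It adds health literacy, measured by the Newest Vital Sign. It does not say that any of these will be in a model, and it does not list pre-visit blood pressure, hemoglobin A1c or LDL cholesterol.

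For the clinical measures, Methods/Design says: "At 6 months, a chart abstraction will be conducted to extract clinical surrogate outcome data". Pre-visit values are not mentioned. The Abstract and the aims call these outcomes exploratory.

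**The concern.** Patients are individually randomised, so a baseline difference between arms is a chance event and a balance test can only measure that chance. The value of adjusting for a covariate depends on how well it predicts the outcome, and the balance test carries no information on that. Two consequences follow.

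- **The model is not fixed.** Which covariates are noted depends on the realised data and, with no threshold given, on the analyst's judgement. Several different adjusted estimates of the same effect are open for every outcome, including medication understanding, on which the trial was sized.
- **Precision is given up.** A strong predictor that happens to be balanced is left out, although including it would reduce the standard error (identity link) or raise power (logit link). The article itself reports that limited literacy and limited English proficiency go with poorer medication understanding. Yet under the rule these two enter only if they are noted as differing between arms.

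**Working it through.** **Inputs.** From the Analyses section: 300 per arm, a difference of 3 mm Hg in systolic blood pressure, SD 12, stated power 86%. Assumed, because the article does not give them: two-sided alpha 0.05, no dropout, a correlation r of 0.3, 0.5 or 0.7 between the pre-visit and 6-month value, and a covariate counted as noted when its baseline p-value is below 0.05.

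**Step 1: reproduce the stated power.** The standard error of the difference is 12 × √(2/300) = 0.980. Then 3/0.980 = 3.062 and Φ(3.062 − 1.960) = 0.865. This matches the stated 86%. A one-sided test would give 92.2%, so the stated figure is a two-sided, unadjusted comparison.

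**Step 2: how often the rule picks a covariate.** Under randomisation a given covariate is flagged 5% of the time (simulated: 4.7% to 4.9%), so it is left out about 95% of the time however prognostic it is. With k independent covariates, the chance that at least one is flagged is 1 − 0.95^k: 34% for k = 8 and 46% for k = 12.

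**Step 3: power if the pre-visit value is always in the model.** The residual SD is 12 × √(1 − r²), and power is Φ(3 / [residual SD × √(2/300)] − 1.960).

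- r = 0.3: SD 11.45, Φ(3.210 − 1.960) = 89.4%
- r = 0.5: SD 10.39, Φ(3.536 − 1.960) = 94.2%
- r = 0.7: SD 8.57, Φ(4.287 − 1.960) = 99.0%

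Equivalently, the number per arm that gives the unadjusted power falls to 300 × (1 − r²): 273, 225 and 153.

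**Step 4: the rule itself.** This step takes the case most favourable to the rule, in which the pre-visit value is among the variables tested. In 15,000 simulated trials per scenario, the baseline value was compared between arms by t test. The outcome was analysed with the baseline value as covariate if p < 0.05, and unadjusted otherwise. Monte Carlo standard errors are about √(0.87 × 0.13/15,000) = 0.3 points for power and √(0.05 × 0.95/15,000) = 0.2 points for type I error.

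A large-sample formula serves as a check: P(reject) = P(|Z| ≤ 1.96 and |U| > 1.96) + 0.05 × P(|A| > 1.96). Z is the baseline z-statistic. U is the unadjusted statistic, which has correlation r with Z. A is the adjusted statistic, which is independent of Z. At r = 0.5 with a true 3 mm Hg difference this is 0.828 + 0.05 × 0.942 = 0.875.

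| r | Unadjusted power | Prespecified power | Rule: power, simulated (formula) | Rule: type I error, simulated (formula) |
|---|---|---|---|---|
| 0.3 | 86.5% | 89.4% | 86.5% (86.9%) | 5.0% (4.8%) |
| 0.5 | 86.5% | 94.2% | 87.7% (87.5%) | 4.4% (4.3%) |
| 0.7 | 86.5% | 99.0% | 88.1% (88.3%) | 3.6% (3.6%) |

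At r = 0.5, prespecified adjustment gains 94.2 − 86.5 = 7.7 points, and by the formula the rule keeps 87.5 − 86.5 = 1.0 point of that. Type I error falls below 5% because the large imbalances are adjusted away, while the remaining trials still carry the full unadjusted standard error.

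**The case against.** The strongest reply is that all the quantified loss falls on an outcome the protocol calls exploratory, whose unadjusted power of 86% is already adequate, and that the size rests on a correlation the article does not give. That stands. No calculation was made for the four key outcomes, and the figures above are an illustration.

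A second reply is that a full covariate list commonly sits in an analysis plan, which is not shown. That is true, and the absence of a list is not the point. The article states a selection rule, and an analysis plan that followed it would carry the flaw forward.

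Several stronger readings are tempting but not supported:

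- **That covariates enter only if p < 0.05.** The text says noted and gives no threshold; 0.05 is an assumption made here. A looser criterion would still be data-driven.
- **That the rule inflates false positives or miscalibrates standard errors for all outcomes.** In the case examined it is conservative, and negligibly so at r = 0.3. The logit models were not examined.
- **That pre-visit blood pressure, hemoglobin A1c and LDL are available in the chart and were left out.** The article neither lists them as collected nor says that the chart holds them. They may not even reach the balance tests.
- **That the stated 86% is wrong.** It reproduces.
- **That an LDL model with treatment arm alone is specified.** LDL is absent from the article's list of identity-link outcomes.

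**Conclusion.** The concern holds as a flaw in a stated rule. Choosing covariates from a comparison of randomised arms leaves the model for every outcome dependent on chance and judgement, and will usually omit strong predictors. The harm is forgone precision and an unfixed model; it is not a false-positive problem or an error in a stated figure.

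On the exploratory systolic pressure outcome the forgone power is roughly 3 to 11 points (89.4% against about 87% at r = 0.3; 99.0% against about 88% at r = 0.7). This rests on the assumed correlation, a two-sided 0.05 test, a 0.05 flag, full follow-up, and a pre-visit value being available. For medication understanding, reconciliation, regimen consolidation and adherence, the data dependence follows from the text alone, but its effect on power is not quantified. The rule should be changed before analysis; the design and the sample size are unaffected.

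**What to change.** Delete the sentence that takes covariates from the descriptive analysis. In its place, name before analysis a short set of prognostic covariates already collected or known at enrolment, included in every model whatever the observed balance. Health literacy, English proficiency or language, age and clinic are reasonable examples; the choice belongs to the investigators. The baseline table can stay as description, without tests that drive the models.

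For the exploratory clinical outcomes, add the last value before the index visit as a covariate where the chart holds one. Prespecify how missing or old values will be handled.

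The cost is a wording change, a few extra chart-abstraction fields, and some patients with no usable baseline laboratory value. In the logit models the adjusted odds ratio is conditional on the covariates and differs from the marginal one, so the plan should say which is being reported. The Trial status section describes enrolment as still open, so the change can be made without touching recruitment or treatment.
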